**Methods:**

This non-inferiority, effectiveness–implementation hybrid type III trial uses a cluster-randomized controlled design, with LTCFs as the unit of randomization. Forty German-speaking LTCFs in Switzerland (≥20 long-term care beds; cantonal accreditation) will be randomized (1:1) after formal consent to either individualized or collective implementation support, without blinding of LTCFs or the research team. In the individualized arm (20 LTCFs), leadership receives 1:1 support meetings, and INTERCARE nurses receive 1:1 coaching, mirroring the original INTERCARE trial. In the collective arm (20 LTCFs), leadership support and INTERCARE nurse coaching are delivered in group formats involving several LTCFs/INTERCARE nurses together at two-monthly intervals. The primary outcome is LTCF-level fidelity to the INTERCARE core components, analyzed with a binomial generalized linear mixed model including a random LTCF effect. Non-inferiority of the collective mode will be concluded if the lower bound of its 95% confidence interval for fidelity is within 15% of the individualized mode. A 12-month cost-effectiveness analysis from a multi-stakeholder perspective (LTCFs and research group) will estimate the incremental cost-effectiveness ratio using differences in implementation costs and unplanned transfers between arms; secondary outcomes include unplanned transfers, staff turnover, and absences.

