### Sample size and inclusion criteria

LTCFs will be recruited via LTC national and professional associations, magazines, direct contact, and snowballing. The sample size calculation assumes a 15% difference in overall fidelity between trial arms (65% vs. 80%). Based on a simulation with 2,000 iterations, a between-cluster variance of 0.1 (ICC = 0.029), and a two-sided alpha of 0.025, 18 LTCFs per arm provide 84% power to detect a 15% difference; for a 20% difference, power increases to 97%. Allowing for a 10% loss between consent and allocation, and after intervention start, the target sample is 40 LTCFs (20 per arm) (Fig. 5).

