**Implementation outcome**											
Overall fidelity score (intervention phase) (aim 1)	LTCF leadership	Semi-structured interview (quan. and qual. data)	x	x	x	x	x				
Fidelity to core components (aim 2.1):											
a) Interprofessional collaboration	INTERCARE nurse, LTCF staff	Online survey	x		x		x				
	Physicians				x		x				
b) INTERCARE nurse	INTERCARE nurse	Structure report about coaching activities (qual. data)		x	x	x	x	x	x	x	x
		Observations (qual. data)			x						
c) Comprehensive Geriatric Assessment	LTCF leadership	Structure report about activities related to CGA (qual. data)					x				
d) Evidence-based tools	LTCF staff	Online survey	x		x		x				
	Physicians				x		x				
e) Advance Care Planning	Residents (reported by LTCF leadership/INTERCARE nurse)	Excel data sheet	x	x	x	x	x	x	x	x	x
f) Data-driven quality improvement	LTCF leadership/project team	Structured report about activities related to data-driven quality improvement (qual. data)					x				
Sustainability (aim 2.1)	LTCF leadership	Semi-structured interview (quan. and qual. data)						x	x	x	x
Acceptability (aim 2.1)	LTCF leadership (only T0 and T4), INTERCARE nurse, LTCF staff	Online survey	x		x		x				
Feasibility (aim 2.1)	LTCF leadership (only T0 and T4), INTERCARE nurse, LTCF staff	Online survey	x		x		x				

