**Effectiveness outcomes**											
Unplanned transfers (aim 2.3a)	Residents (reported by LTCF leadership/INTERCARE nurse)	Excel-based quality monitoring tool	x	x	x	x	x	x	x	x	x
Staff turnover (aim 2.3b)	LTCF leadership	LTCF routine data/exports from staff rosters	x	x	x	x	x	x	x	x	x
Staff absences (aim 2.3b)	LTCF leadership	LTCF routine data/exports from staff rosters	x	x	x	x	x	x	x	x	x
Staff intent to leave (aim 2.3b)	LTCF staff	Online survey	x		x		x				

T0 to T8 refer to timepoints from baseline (T0) to start of intervention (T1, one month after T0) followed by three-monthly data collection points (T2 to T8)

*Abbreviations*: *LTCF* long-term care facility

^a^ Data is quantitative unless otherwise marked

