#### Implementation outcomes (aims 1 and 2.1)

Overall fidelity to INTERCARE core components (primary outcome, aim 1) will be assessed via semi-structured interviews with LTCF leadership every three months. Two researchers (one interviewer, one note-taker) will review each minimal requirement and classify it as systematically, partially, or not (yet) implemented, yielding an overall fidelity score (percentage of minimal requirements implemented as intended) at each time point. Fidelity will be interpreted as high (80–100%), moderate (51–79%), or low (0–50%), following published cut-offs [59, 60].

For aim 2.1, fidelity will also be measured separately for each core component using: 1) online surveys of INTERCARE nurses, LTCF staff, and physicians (interprofessional collaboration and evidence-based tools); 2) structured reports from LTCF leadership (comprehensive geriatric assessment and data-driven quality improvement); 3) structured reports and observation of INTERCARE nurses’ coaching activities; 4) and Excel data sheets reporting ACP conversations with newly admitted residents, at time points defined in Table 2. Sustainability will be assessed by overall self-reported fidelity over 12 months post-implementation.

Acceptability and feasibility of selected core components will be assessed with the Acceptability of Intervention Measure (AIM) and Feasibility of Intervention Measure (FIM) [61]. INTERCARE nurses and LTCF staff will complete online surveys at T0, as well as 6 and 12 months after intervention start (T2, T4), while leadership will be surveyed at T0 and T4 (cf. Table 2).

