### Data analysis

All quantitative data will be analyzed using R 4.5.x [70]. Descriptive statistics will summarize implementation, economic, and effectiveness outcomes and sample characteristics (means and standard deviations or medians and interquartile ranges for continuous variables, and frequencies and percentages for categorical variables). Multiple imputation will be considered depending on the extent of missing data [71]. Following CONSORT for cluster-RCTs [51], baseline differences between arms at the LTCF level will be presented using standardized mean differences and, where appropriate, frequencies and percentages.

For aim 1 (fidelity) and aim 2.1 (acceptability and feasibility), the non-inferiority margin is set at 15%. The non-inferiority of collaborative versus individualized support will be tested using binomial generalized linear mixed models with a random effect for LTCFs, and 95% confidence intervals; non-inferiority is confirmed if the lower confidence bound does not cross 15% below the arm II value.

A convergent mixed-methods approach will be used for aim 2.1. Qualitative data (interview notes, coaching activities reports, RAP sheets) will be analyzed using framework analysis [72, 73]. combining inductive and deductive themes to identify patterns in INTERCARE nurses’ practices and coaching approaches in acute situations. Qualitative findings will be compared with quantitative fidelity trajectories to explore fidelity moderators, and observational data will be coded in MAXQDA (https://www.maxqda.com/).

For aim 2.2, descriptive analyses will summarize intervention, implementation, and hospitalization costs by arm. A cost-effectiveness analysis will estimate the ICER, defined as the difference in costs between the two modes of delivery divided by the difference in their effects, measured as the number of unplanned hospital transfers. CEA helps identify ways to redirect resources to more cost-effective approaches [74]. We will use a multi-stakeholder perspective (i.e., LTCF and research group perspectives) and a 12-month time horizon, respecting the NICE guideline while reflecting data availability [75]. One-way sensitivity analysis and scenario analysis will be used to gauge our predictions’ level of uncertainty.

For aims 2.3a and 2.3b, the effects of the two delivery modes on unplanned transfers and staff outcomes will be analyzed using mixed-effects models analogous to those for aim 2.1, accounting for clustering at LTCF level.

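### Fidelity is scored at five visits (T0–T4), but the plan does not say which visit or summary the 15% non-inferiority margin applies to, nor how the T0 score is used

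*Protocol article*

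**What the plan says.** All places are in the protocol article.

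- **Outcome.** The section on implementation outcomes has two researchers classify each minimal requirement from three-monthly leadership interviews, "yielding an overall fidelity score (percentage of minimal requirements implemented as intended) at each time point".
- **Visits.** Table 2 marks the row "Overall fidelity score (intervention phase) (aim 1") at T0, T1, T2, T3 and T4.
- **Model.** Data analysis says that non-inferiority will be "tested using binomial generalized linear mixed models with a random effect for LTCFs, and 95% confidence intervals". The Abstract says that the outcome is "analyzed with a binomial generalized linear mixed model including a random LTCF effect". Neither sentence names a visit, a summary over visits, or any role for the T0 score.
- **Margin.** Data analysis states that "the non-inferiority margin is set at 15" per cent.
- **Visit timing.** The Table 2 footnote runs from "baseline (T0) to start of intervention (T1, one month after T0) followed by three-monthly data collection points (T2 to T8"). The implementation outcomes section places the acceptability and feasibility surveys at T0, "as well as 6 and 12 months after intervention start (T2, T4").
- **Blinding.** Under Randomization, researchers and facilities know the allocation once a cohort has been assigned.

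**The concern.** The time point is part of the definition of a primary endpoint. This one has five candidate occasions, and averages over them, with none chosen. The article does give time frames for lesser items: 12 months for cost-effectiveness, 12 months after implementation for sustainability, and named visits for acceptability and feasibility.

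The choice matters because the margin is fixed while the arm difference is likely to change over the visits. No effect of the support mode is expected at T0, nor at T1 if T1 is the start of intervention as the footnote says. Averaging those visits with later ones would shrink a deficit that persists or grows, and so favour non-inferiority. Averaging would penalise a deficit that closes by T4. Either way, the conclusion could turn on a decision taken after unblinded fidelity ratings have been seen.

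Separately, T0 fidelity is collected in every facility and the described model does not visibly use it, although only 40 facilities are to be randomised.

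**Working it through.** **1. The plan's own figures.** The inputs, from the sample size section, are 65% vs 80%, between-cluster variance 0.1 (ICC 0.029), two-sided alpha 0.025, 18 facilities per arm, 84% power (97% for a 20% difference) and 10% loss.

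- ICC = 0.1 / (0.1 + π²/3) = 0.1 / 3.390 = 0.0295, which agrees with 0.029.
- Target: 18 / (1 − 0.10) = 20 per arm, 40 in total, which agrees.
- Power depends on m, the number of requirements scored per facility, which the text at hand does not give. The effective number of ratings per arm is 18m / (1 + (m − 1) × ICC). For m = 14 this is 252 / 1.383 ≈ 182.

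| m | Power, 65% vs 80% (formula and simulation) |
|---|---|
| 10 | 73% |
| 12 | 79–80% |
| 13 | 81–83% |
| 14 | 84–85% |
| 20 | 92–94% |

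At m = 13–14, 60% vs 80% gives 97–98%. Both stated powers therefore fit one score per facility with about 13–14 items. They cannot be confirmed without m. The fit suggests that one occasion was planned, but that occasion is not named.

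**2. Visit timing.** By the footnote, T1 is 0, T2 is 3, T3 is 6 and T4 is 9 months after intervention start. By the outcome section, T2 is 6 and T4 is 12 months. The two cannot both hold.

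**3. Arithmetic of averaging.** Take a true T4 deficit of 15 points, exactly at the margin (read as percentage points). The average deficit is 15 multiplied by the mean fraction of the deficit present at the visits included.

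| Assumed path of the deficit | Fractions at T0…T4 | T0–T4 mean | T1–T4 mean |
|---|---|---|---|
| Linear from T0 | 0, ¼, ½, ¾, 1 | 0.5 × 15 = 7.5 | 0.625 × 15 = 9.4 |
| None until T1, then linear | 0, 0, ⅓, ⅔, 1 | 0.4 × 15 = 6.0 | 0.5 × 15 = 7.5 |
| Full from T2 on | 0, 0, 1, 1, 1 | 0.6 × 15 = 9.0 | 0.75 × 15 = 11.3 |

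**4. Effect on the non-inferiority decision.** The simulation used 18 facilities per arm, m from 12 to 30, a logit-normal facility effect with variance 0.1, both arms at 30% at T0, and 80% vs 65% at T4. A 95% t interval on facility means stood in for the mixed model. Non-inferiority was declared if the lower bound lay above −15 points.

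| Path | T4 only | T1–T4 averaged | T0–T4 averaged |
|---|---|---|---|
| Linear from T0 | 2.4–2.6% | 38–50% | 65–79% |
| None until T1, then linear | 2.3–2.7% | 62–77% | 83–92% |
| Full from T2 on | as above (same T4 rates) | 20–27% | 49–62% |

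The nominal figure at the margin is 2.5%.

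**5. The reverse case.** If the collaborative arm lags early, with an average shortfall of 10 points over T0–T4, and is level by T4, non-inferiority is declared in 94–99.8% of trials at T4 alone and in 38–50% on the T0–T4 average.

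**The case against.** The strongest reply is that this is a condensed article and its model sentence is not a full specification. It does not list even the arm effect, without which there is no comparison. A reader might infer that the model contains nothing but a random facility effect, or that repeated ratings of one requirement are treated as independent. The text supports neither inference. Visit terms, covariates and correlation structure are commonly left to the analysis plan. That reply stands.

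A reader might also infer that T0–T4 will be pooled. The article does not say so. The sample size, with one proportion per arm and one variance component, points towards a single occasion. Data analysis also speaks of comparing qualitative findings with fidelity trajectories, which treats fidelity as changing over time. That stands too, so the percentages above describe an analysis the text leaves open, not one it announces.

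Nor is the bias always towards non-inferiority, as the catch-up case shows. Omitting T0 from a randomised comparison does not bias it; the loss is in precision. In addition, baseline differences between arms are to be presented as standardized mean differences, and facilities already working with INTERCARE nurses and at high fidelity are excluded, which limits baseline spread.

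None of this supplies the missing item. The article does not state the occasion to which the margin applies, and that belongs to the definition of the primary endpoint rather than to modelling detail.

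**Conclusion.** The point holds in a limited form. The primary outcome has five scheduled scores and no named visit or summary for the non-inferiority test, no stated use of the T0 score, and two incompatible timings for T4.

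The possible size is large but conditional. With a true 15-point deficit at T4, false declaration of non-inferiority is about 2.5% at T4 alone and roughly 49–92% if T0–T4 were averaged (20–77% for T1–T4). These figures rest on assumptions that are not in the document: 12 to 30 requirements, a 30% starting level, the three trajectories, a margin in percentage points, and a facility-level t interval in place of the mixed model. The direction reverses if an early deficit closes by T4. What is established is that the conclusion can depend on a choice left open in an unblinded trial, not that the plan will pool visits or is biased in one direction.

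**What to change.** 1. State the primary estimand as the difference in fidelity, collaborative (arm II) minus individualized (arm I), at the end-of-intervention visit, T4.
2. Estimate it from the binomial mixed model already planned, with each facility's T0 fidelity as a covariate. The reason is precision.
3. Use T1–T3 only in a secondary model with an arm-by-visit term.
4. Reconcile the timing of T4 between the Table 2 footnote (9 months after start) and the implementation outcomes section (12 months). Until that is done, naming T4 does not fix a time point.
5. State that the sample size refers to this visit, and give the number of requirements scored per facility.

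The cost is wording in the protocol and analysis plan. No new data are needed, because every score is already scheduled. The change should be dated before any comparison of fidelity by arm.

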### Implementation strategies, mode of delivery, and study arms

In WP1, implementation strategies were specified and differentiated between the two study arms (Fig. 3). Strategies target LTCF model implementers, LTCF leadership (e.g., LTCF director, director of nursing), and INTERCARE nurses and are fully described using the AACTT framework [50] in Supplementary Material 2.

The key contrast between arms is the mode of delivery of support meetings for LTCF model implementers and coaching for INTERCARE nurses. In arm I (individualized support), support meetings with LTCF model implementers and coaching sessions with INTERCARE nurses are held separately for each LTCF and for each INTERCARE nurse, respectively. In arm II (collaborative support), LTCF model implementers and INTERCARE nurses are grouped across LTCFs within the same cohort arm for joint support and coaching sessions.

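### The Methods rule for primary non-inferiority takes arm II, the arm under test, as its reference; the abstract takes the other arm but ignores that arm's sampling error

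*Protocol article*

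**What the plan says.** The section on implementation strategies and study arms fixes the labels: "In arm I (individualized support), support meetings with LTCF model implementers and coaching sessions with INTERCARE nurses are held separately", and "In arm II (collaborative support), LTCF model implementers and INTERCARE nurses are grouped across LTCFs within the same cohort arm". Arm I is therefore the reference and arm II the arm under test.

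Data analysis gives the hypothesis in that direction: "The non-inferiority of collaborative versus individualized support will be tested using binomial generalized linear mixed models with a random effect for LTCFs". For aim 1 (fidelity) and for acceptability and feasibility under aim 2.1, it states that "the non-inferiority margin is set at 15" per cent. The sentence on the hypothesis ends with the criterion: "non-inferiority is confirmed if the lower confidence bound does not cross 15% below the arm II value".

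The Methods paragraph of the abstract gives the criterion differently. The collective mode is non-inferior if "the lower bound of its 95% confidence interval for fidelity is within 15% of the individualized mode".

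The sample size section assumes fidelity of 65% against 80%, a between-cluster variance of 0.1 (ICC 0.029) and 18 LTCFs per arm, raised to 20 for 10% loss.

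**The concern.** A non-inferiority limit belongs below the reference arm. Data analysis places it below the arm under test, and the abstract places it below the other arm. One analysis cannot follow both sentences.

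The abstract's version has a separate weakness. It takes the confidence interval of one arm alone and sets it against the other arm's value. The individualized value is itself estimated from about 18 to 20 facilities, and its sampling error does not enter the comparison.

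The criterion decides the primary aim and is reused for acceptability and feasibility. With two published versions, the conclusion could be disputed, or a version chosen, once the data are known.

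**Working it through.** **Inputs.** From the sample size section: n = 18 LTCFs per arm, between-cluster variance 0.1 on the log-odds scale, fidelity 80% and 65%. From Data analysis: a 15% margin and 95% intervals. The number of minimal requirements per LTCF, m, is the binomial denominator of the fidelity score. The article does not give it, so it is assumed, with a range of 10 to 20.

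**The plan's own figures first.**
- ICC = 0.1 / (0.1 + π²/3) = 0.1 / 3.39 = 0.0295, in line with the stated 0.029.
- Allowance for loss: 18 / (1 − 0.10) = 20 per arm, as stated.
- Power, simulated with logit-normal binomial data and a cluster-level t-test: m = 14 at two-sided alpha 0.025 gives 84.0% (65% vs 80%) and 97.5% (60% vs 80%), against the stated 84% and 97%. At two-sided 0.05, m = 11 gives 84.2% and 97.0%. The stated power is attainable but cannot be confirmed without m.

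**Methods rule, arm II's bound against arm II's own value.** The criterion reduces to whether the half-width of arm II's interval is below 15 points. Arm I does not enter. The standard error of one arm is

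SE(p) = √[ p(1−p)/(n·m) + (p(1−p))²·0.1/n ].

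The widest case in the range is m = 10, p = 0.5: √(0.25/180 + 0.0625 × 0.1/18) = √(0.001389 + 0.000347) = 0.0417. The half-width is 1.96 × 0.0417 = 8.2 points, or 8.8 points with the t multiplier 2.11 for 17 degrees of freedom. Both are well under 15, so the rule is met whatever arm I achieves.

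**Methods rule, arm I's bound against the arm II value minus 15 points.** This asks whether arm I is not much worse than arm II, which is the reverse question.

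**Abstract rule.** When the true difference is exactly 15 points, the chance of a false conclusion is approximately

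1 − Φ( 1.96 × SE_II / √(SE_I² + SE_II²) ).

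With m = 14: SE_I² = 0.16/252 + 0.0256 × 0.1/18 = 0.000777, and SE_II² = 0.2275/252 + 0.05176 × 0.1/18 = 0.001190. The ratio is √(0.001190/0.001967) = 0.778, then 1.96 × 0.778 = 1.52, and the error is 6.4%. It is 6.4% at m = 10 and 6.3% at m = 20.

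**Simulation of all rules** (m = 14, 18 LTCFs per arm, 40,000 runs, t-based intervals on cluster proportions as a stand-in for the GLMM). Entries are the probability of concluding non-inferiority.

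| True fidelity, arm I / arm II | CI of the difference above −15 points | Methods, arm II against itself | Methods, arm I's bound | Abstract |
|---|---|---|---|---|
| 80 / 80 | 95.8% | 100% | 98.3% | 98.2% |
| 80 / 65 | 2.7% | 100% | 100% | 7.0% |
| 80 / 60 | 0.2% | 100% | 100% | 0.6% |
| 80 / 40 | 0% | 100% | 100% | 0% |
| 65 / 80 | 100% | 100% | 7.1% | 100% |

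At 80 / 65, m = 11 and m = 20 give 2.6% and 2.7% for the difference rule, and 7.0% and 6.9% for the abstract rule. In these runs the fidelities were set at the median facility. Averaged over facilities they came to 79.5% and 64.7%, slightly inside the margin. With the averages set exactly at 80% and 65% and m from 10 to 20, a further simulation gives 2.4–2.5% for the difference rule. The abstract rule then gives 6.5–6.6% with t-based intervals and about 8% with z-based ones.

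**The case against.** The best defence is that this is a labelling slip. The hypothesis half of the same sentence runs in the right direction, so do the background and central hypothesis, and the abstract names the individualized mode. The sentence also specifies a mixed model of collaborative versus individualized support and does not say whose bound is meant, so a between-arm contrast may have been intended. That is plausible and it limits the point. Two inferences should not be drawn.

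- A reader might infer that neither version uses an interval for the between-arm difference. This is explicit only in the abstract, which speaks of the collective mode's own interval. The Methods sentence leaves it open.
- A reader might infer that the trial will be analysed by a rule that cannot fail. The 100% figure shows that the sentence is unusable as worded. It does not predict what the analysts will do.

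The slip still needs correcting, because it sits in the operative sentence for the primary aim. Changing the label alone would also leave a bound set against an arm's value, as in the abstract. Nor is this a detail left to a SAP: the article states the rule, and states it two ways.

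A reader might also take the 15% as relative, giving a limit of 80% − 12 points = 68%. The documents do not support this. The sample size section uses 15% for 65% against 80%, which is percentage points, and nothing suggests a relative margin. Naming the unit is a matter of clarity only.

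**Conclusion.** The point holds. The Methods criterion names the arm under test as the reference and conflicts with the abstract; this needs no assumption beyond the article's own arm labels. Taken literally, it is either met in about 100% of trials or runs in reverse. The abstract's criterion tests in the right direction, but at the margin its one-sided error is about 6.5–8% (about 6.5–7% with t-based intervals) instead of about 2.5%. The upper end reflects z-based intervals with only 18 clusters.

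These rates rest on 18 LTCFs per arm, a between-cluster variance of 0.1, an assumed 10 to 20 minimal requirements per LTCF, and cluster-level intervals in place of a fitted GLMM. They hardly change over that range. Because this is the decision rule for the primary aim, it must be corrected before the data are analysed.

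**What to change.** Use one sentence in the abstract and in Data analysis: *Non-inferiority of arm II (collaborative support) is concluded if the lower limit of the two-sided 95% confidence interval for the difference in fidelity, arm II minus arm I, estimated from the binomial mixed model on the risk-difference scale, lies above −15 percentage points.* The same form should serve acceptability and feasibility, where the article applies the same margin. How the interval is obtained from a model fitted on the log-odds scale can be left to the SAP.

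The cost is wording in two places and a few lines of code, with no new data. The sample size need not change because of this: with 18 LTCFs per arm and both arms truly at 80%, the difference rule concludes non-inferiority with probability 91.5% (m = 11), 95.8% (m = 14) and 98.8% (m = 20). With both at 65% the figures are 78.4%, 85.6% and 93.1%.

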## Abstract

**Background:**

Over recent decades, multifaceted nurse-led care models have been developed to reduce unplanned hospital transfers from long-term care facilities (LTCFs). In Switzerland, the INTERCARE model has demonstrated effectiveness, with core components including deployment of nurses in expanded roles (INTERCARE nurses), evidence-based communication tools, and advance care planning. However, resource-intensive implementation strategies such as 1:1 support meetings for model implementers pose challenges for scale-up, underscoring the need for more scalable implementation support. The INTERSCALE study compares two modes of delivering implementation support—an individualized and a collective-oriented approach—testing the hypothesis that the latter achieves non-inferior fidelity to the INTERCARE model and comparable reductions in unplanned hospital transfers at the LTCF level. Secondary aims are to compare implementation (acceptability, feasibility), economic (costs, cost-effectiveness), clinical (unplanned transfers), and organizational (staff absences, turnover) outcomes.

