**Fig. 2 Fig2:**
[figure not shown]
The INTERSCALE study

The central hypothesis is that replacing individual LTCF support with group-based support, and one-to-one INTERCARE nurse coaching with collaborative coaching, will reduce costs by minimizing the time investment of the support system (research team and external facilitators), while maintaining fidelity to the care model at LTCF level and preserving its clinical effect in reducing residents’ unplanned transfers.

The Exploration, Preparation, Implementation, Sustainment (EPIS) framework guides INTERSCALE [45]. WP1 corresponds to the preparation phase, in which minimal requirements of the core components were adapted and implementation strategies – along with the two delivery modes to be compared – were defined; WP2 covers the LTCFs’ preparatory, implementation, and sustainment phases.

Several methodological considerations informed the development of implementation strategies for WP2. Four workshops were conducted with LTCFs that had participated in INTERCARE and those interested in INTERSCALE. Using an implementation mapping approach [46], strategies were adapted to enhance adoption, implementation, and sustainability of the INTERCARE model. The minimal requirements for each core component were reviewed to focus on essential functions and distinguish these from the various ways components may be operationalized in practice [47], followed by adaptations using the FRAME method to align the model and strategies with the Swiss context [48]. In the first workshop, LTCFs identified barriers and facilitators and suggested adaptations. Performance objectives were then defined to address these barriers (see Supplementary Material 1), and the COM-B model and the Theoretical Domains Framework (TDF) were applied to identify behavioral determinants [49]. Finally, implementation strategies were adapted based on these determinants and described using the action, actor, context, target, time (AACTT) framework of Presseau and colleagues [50], resulting in a set of clearly specified strategies to be examined in the planned cluster-RCT (see Supplementary Material 2).

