### Aims

The overall aim of INTERSCALE is to compare two modes of delivery for support and coaching (individualized vs. collaborative) to help LTCFs adopt and implement the INTERCARE model. This includes assessing implementation outcomes, calculating cost-effectiveness, and evaluating overall effectiveness. Specifically, the aims are:Primary outcome: To compare the individualized vs. collaborative arm in relation to LTCFs’ overall fidelity to the INTERCARE model (aim 1).Secondary implementation outcomes: To compare the two modes of delivery in relation to further implementation outcomes, i.e., LTCFs’ fidelity to the six single core components of the INTERCARE model, sustainability of the INTERCARE model, as well as the model’s acceptability and feasibility (secondary aim 2.1).Economic outcome: to assess the costs of the implementation strategies and to calculate the incremental cost-effectiveness ratio (ICER) of implementing the INTERCARE model in LTCFs. This will involve comparing the two modes of delivery from both the LTCFs' and the research team's perspectives, with the number of unplanned hospital transfers of LTC residents as the effectiveness outcome (secondary aim 2.2).Effectiveness outcomes:oTo assess the effect of the two modes of delivery on clinical effectiveness, specifically unplanned transfers of LTCF residents (secondary aim 2.3a).oTo assess the effect of the two modes of delivery on organizational outcomes, such as staff absences and staff turnover (aim 2.3b).

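### If the two arms have similar unplanned transfers, as hypothesised, the ICER for aim 2.2 has a near-zero denominator, and the named uncertainty analyses do not carry joint sampling error

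*Protocol article*

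**What the plan says.** Data analysis (aim 2.2) defines the ICER as "the difference in costs between the two modes of delivery divided by the difference in their effects". The effect is the number of unplanned hospital transfers. Aims agrees, describing the economic comparison "with the number of unplanned hospital transfers of LTC residents as the effectiveness outcome", and so does the abstract's Methods paragraph.

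The hypothesis appears in two places. The abstract's Background expects the collective mode to achieve "comparable reductions in unplanned hospital transfers at the LTCF level". The central hypothesis, in the section on the INTERSCALE study, expects lower cost while "preserving its clinical effect in reducing residents’ unplanned transfers".

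On economic uncertainty, the sentence beginning "One-way sensitivity analysis and scenario analysis will be used to gauge our" names two methods and no others. Data analysis also plans descriptive cost summaries by arm (aim 2.2) and mixed-effects models of transfers that allow for clustering by LTCF (aim 2.3a). Effectiveness and organizational outcomes sets the transfer indicator as a rate per 1,000 care days.

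**The concern.** The hypothesis and the chosen ratio pull against each other. A delivery mode that saves money and leaves transfers unchanged is the result the trial hopes for, and it is the one for which a cost-per-transfer ratio behaves worst. Small chance differences in transfers then decide the ratio's size and sign.

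The sign alone does not identify the result either. If the effect is counted as transfers avoided, a negative ratio can mean cheaper with fewer transfers, or dearer with more. If it is counted as raw transfers, those same two opposite outcomes share a positive ratio.

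One-way and scenario analyses vary inputs deterministically. They do not show how far costs and transfers, taken together, could move by sampling about 40 facilities. At stake is whether the cost-effectiveness result can be read at all if the hypothesis holds.

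**Working it through.** The article gives no expected rate, variance, margin or power for transfers, costs or the ICER, so there is no figure of its own to reproduce. The 84% power concerns fidelity and does not bear on this point.

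**Inputs from the article.** 20 LTCFs per arm (Sample size); about 4,000 residents (Table 1), so 4,000 / 40 = 100 per LTCF; a 12-month horizon, so 100 × 365 = 36,500 care days per LTCF.

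**Assumed, because not given.** Transfer rate 0.5, 1 or 2 per 1,000 care days; between-LTCF coefficient of variation (CV) 0.3 or 0.5; true rate ratio (collective over individualized) 1.00, 1.05, 1.10 or 1.30; a saving of 1 cost unit per LTCF with SE 0.25.

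**Step 1: the general result, which needs no assumed rates or costs.** Write dC and dE for the estimated cost and transfer differences, with variances V_C and V_E and covariance V_CE. The 95% Fieller set holds all R with (dC − R·dE)² ≤ 1.96²·(V_C − 2R·V_CE + R²·V_E). The coefficient of R² is dE² − 1.96²·V_E, so the set is bounded only if |dE| / SE(dE) > 1.96. If transfers are truly equal, that happens in 5% of trials, so the set is unbounded in 95%. P(dE > 0) = 0.5, so for a given cost saving the sign of the ratio is a coin toss.

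**Step 2: SE of the denominator, at 1.0 per 1,000 days and CV 0.3.** The mean is 36.5 transfers per LTCF. The variance is 36.5 + (0.3 × 36.5)² = 36.5 + 119.9 = 156.4. SE(dE) = √(2 × 156.4 / 20) = 3.95 transfers per LTCF, which matches the simulated SD.

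**Step 3: how fast the problem fades.** There were 40,000 simulated trials per scenario, with gamma-Poisson transfers; trials with dE exactly zero have no ratio and were dropped from the ICER ranges. Columns 3 to 5 are for the Step 2 scenario. Column 5 uses the normal approximation P(|Z + mean/SD| > 1.96).

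| True rate ratio | P(dE > 0), all six rate and CV scenarios | Mean dE (SD) | Central 95% range of ICER, cost units per transfer | P(Fieller set bounded) |
|---|---|---|---|---|
| 1.00 | 0.49–0.50 | −0.03 (3.95) | −3.71 to +3.65 | 0.05 |
| 1.05 | 0.61–0.68 | 1.84 (4.03) | −3.44 to +3.13 | 0.07 |
| 1.10 | 0.71–0.83 | 3.65 (4.15) | −2.46 to +2.39 | 0.14 |
| 1.30 | 0.94–0.995 | 10.94 (4.50) | −0.38 to −0.04 | 0.68 |

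For example, at 1.10: 3.65 / 4.15 = 0.88, and P(Z > 1.08) + P(Z < −2.84) = 0.140 + 0.002 = 0.14.

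In all six scenarios the central 95% range covers both signs at rate ratios 1.00 to 1.10. It keeps one sign only at 1.30 with CV 0.3.

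**Step 4: net benefit on the same inputs.** Value a transfer at an assumed 0.1 cost unit, with true dE = 0. The expected net benefit is 1.0. Its SE is √((0.1 × 3.95)² + 0.25²) = √(0.156 + 0.0625) = 0.47, and the 95% range is 1.0 ± 1.96 × 0.47, or about 0.08 to 1.92. It is finite and has a defined sign, from the same data that give an ICER range of −3.71 to +3.65.

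**Step 5: the named uncertainty methods.** A one-way analysis moves one input at a time, and a scenario analysis swaps in a chosen set of inputs. Even if the transfer difference is one of the inputs varied, neither method carries the sampling error of costs and transfers jointly, or their correlation within an LTCF.

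**The case against.** Four counter-arguments deserve weight.

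- **The components are already planned.** Costs are summarised by arm, and transfers get a model that accounts for clustering, so a careful reader could work out the quadrant. This stands, and it limits the damage. It does not supply a stated interval for the cost difference or any joint uncertainty.
- **Comparable does not mean identical.** This stands too. A reader might infer that the ICER is bound to be unstable. The article does not support that: it gives no transfer rate or margin, and the 95% and 50/50 figures hold only at exact equality. A large real loss of clinical effect would make the ratio usable, and an ICER has to be specified before the difference is known. Up to a rate ratio of 1.10, however, the simulated range still covers both signs.
- **A fuller analysis plan may add a bootstrap or net benefit.** It may, and their absence from a condensed article would not by itself be a finding. But this article fixes the ratio and says how its uncertainty will be gauged, and a bootstrapped ratio with a near-zero denominator remains unstable.
- **Ranking net benefit against the ICER is partly presentation.** Agreed, which is why the ICER is kept. Net benefit also needs a value per avoided transfer, which the article does not give.

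**Conclusion.** The concern holds in conditional form, for a secondary aim. If the trial's hypothesis on transfers is true or nearly true, the ICER as defined will have a near-zero denominator, an unstable size and either sign, and the stated uncertainty analyses will not show this adequately. At exact equality the Fieller set is unbounded in 95% of trials whatever the costs. How quickly the problem fades rests on the assumed rates, CVs and costs above: the wrong-sign probability is 17–29% at a rate ratio of 1.10 and about 6% or less at 1.30.

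A reader might also infer that the ICER is the headline economic result, or that a scale-up recommendation would rest on it. The article does not say so. Aim 2.2 also covers the costs of the strategies, the primary outcome is fidelity, and no ICER threshold or decision rule is stated. The change is worth making before analysis, because it is cheap and uses data already being collected.

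**What to change.** Keep the planned summaries and add the following for aim 2.2:

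- Report the cost difference per LTCF and the transfer-rate difference per 1,000 care days, each with a 95% CI.
- Report incremental net benefit over a displayed range of values per avoided transfer.
- Obtain joint uncertainty from a bootstrap that resamples whole LTCFs within arm, keeping each facility's costs and transfers together. Show it on the cost-effectiveness plane with an acceptability curve.
- Keep the ICER. State whether the effect is transfers or transfers avoided, report the ratio with its quadrant, and do not interpret it alone when the transfer difference is compatible with zero.
- Keep one-way and scenario analyses for price and wage inputs.

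The cost is analysis-plan wording and extra code, with no new data. The drawback is that a range of values per avoided transfer has to be assumed for display.
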